#### Health resources usage

The usage of NHS health care and social services for participants will be determined using an adapted health resources questionnaire based on our previous COINCIDE trial [33]. We will obtain information on rates of utilization of most of the major elements of health and social care through linkage with the Salford Integrated Record.

#### Health outcome measures

HbA1c concentrationWeight (kg) and body mass indexQuality of life: measured using the Euroqol-5D-5 L (EQ-5D-5 L) [34]. The five-item EQ-5D-5 L is a generic measure of health-related quality of life, consisting of the EQ-5D descriptive system and the EQ Visual Analogue Scale (EQ VAS). The first part consists of five domains: mobility, self-management, usual activities, pain, anxiety and depression, with five levels of severity for each domain. A utility value can then be calculated based on a population tariff. The visual analogue scale records an individual’s self-perceived health, ranging from 0 to 100.Mental Health Inventory-5: this is a five-item scale that measures general mental health, including depression, anxiety, behavioural-emotional control and general positive affect [35].Health experience and self-management: this will be measured by a modified version of the Summary of Diabetes Self-Care Activities. It assesses the number of days per week respondents engage in healthy and unhealthy behaviours (i.e. eating fruit and vegetable, eating red meat, undertaking exercise, drinking alcohol, and smoking) [36].Patient activation: this will be measured by the Patient Activation Measure. Patient activation is a measurable outcome associated with higher quality of life, improved clinical outcomes and increase engagement with health or social care. The Patient Activation Measure is a self-report measure of patient knowledge, skills and confidence in self-management for long-term conditions [37]. We will use the short 13-item version [38].

#### Routine service level data

We will extract data related to a range of processes associated with engagement with and completion of the intervention from the secure web-based intervention hosted by North West EHealth at the University of Manchester. These data will allow us to assess patient fidelity to the pre-specified service model outlined in Table 1. Specifically, we will run queries to produce aggregate data for all patients in the IGR3 arm at the end of the intervention period related to:Completeness of self-assessmentsNumber of times patients logged in to specific pagesNumber of times patients used ‘contact advisor’ option for additional support

### Sample size

The existing IGR2 service is commissioned for 500 patients per year and we anticipate with the support of Salford Royal NHS Foundation Trust, general practitioners and diabetes specialist nurses to recruit 200 of these patients in 12 months. The trial sample size has therefore been set at 100 patients per arm, based on a pragmatic decision concerning the probable recruitment window. With an estimated 15 % attrition rate, we would have 90 % power to detect an effect on a standardized measure of 0.5 on the CSQ-8, and 70 % power to detect a standardized effect size of 0.4 with a two-sided alpha of 0.05. A significant difference in CSQ-8 scores in favour of IGR3 will prove the hypothesis that the web plus telephone health coaching intervention offers patients a better care experience than the existing telephone-only health coaching intervention.

As a comparison of two active treatments, where one is simply an enhanced version of the other, differences in clinical outcomes, quality of life and cost-effectiveness are expected to be relatively small. Therefore, the trial will not be powered to detect differences for secondary outcomes.

### Eligibility of participants

Participants will be identified from referrals into the existing Impaired Glucose Regulation Care Call service provided by Salford Royal NHS Foundation Trust. Referral criteria into the Impaired Glucose Regulation Care Call service are:Moderate or high risk score on the Diabetes UK Risk score tool [39]

and2.HbA1c = 42–47 mmol/mol (6.0–6.4 %)

or3.Previous diagnosis of impaired glucose regulation with 1× confirmatory blood test (HbA1c within the previous 6 months).

Based on these referral criteria, the eligibility criteria for the trial recruitment are as follows.

#### Inclusion criteria

Aged 18 years or olderHbA1c between 42 and 47 mmol/mol (6.0–6.4 %) in previous 6 monthsAccess to a telephone and home internet

#### Exclusion criteria

Referred to the face-to-face group impaired glucose regulation education session and does not go on to receive telephone-only supportDiagnosis of type 2 diabetes: HbA1c of ≥48 mmol/mol (≥6.5 %)Diagnosis of gestational diabetesDoes not read or speak EnglishIncapable of participating as indicated by general practitioner because of dementia, learning difficulties, vision or motor skills limitations, serious and enduring mental health problems

### Recruitment to the trial

General practice surgeries throughout Salford will be given promotional literature about Care Call (prepared by Hitachi Europe Ltd) to raise awareness among general practitioners about the availability of the service for people with impaired glucose regulation. All patients referred to the Care Call service will have a confirmed diagnosis of impaired glucose regulation and will have had an opportunity to discuss with their general practitioners the options available from the Care Call service. Eligible patients for the service and thus the trial will then be identified from routine contact with patients’ general practitioners.

In addition, a rapid search and find tool designed by NorthWest EHealth, FARSITE, will be used to identify further eligible patients [40]. The FARSITE software provides a safe, convenient and effective way for general practitioners to control the recruitment of their patients into clinical research, while allowing NHS-based researchers to run complex and powerful searches over anonymized population-level health record data. Because FARSITE is hosted in a secure environment located at Salford Royal NHS Foundation Trust, confidentiality of data is preserved. General practitioner data collected and processed for FARSITE are transmitted across the NHS (N3) network, using high grade encryption, by the secured local NHS data host, the General Practitioner System Supplier or Apollo Medical Systems Ltd. Patient demographics data and pseudonymized data are stored in two separated and encrypted databases. In the CATFISH study, a research nurse employed by Hitachi Europe Ltd will run FARSITE searches from general practices in Salford to generate lists of pseudonymized patient populations. The clinical teams in practice can review the selected patients, merge patient contact details using the letter generation tool and send the letters to DocMan for print and postal fulfilment services. These letters will offer patients suspected to have impaired glucose regulation to attend for a general practitioner consultation and onward referral to Care Call.

Feasibility searches using FARSITE protocols for impaired fasting glucose or impaired glucose tolerance were run in November 2014 and identified 3852 patients with suspected impaired glucose regulation. This test run showed that the FARSITE tool was capable of identifying patients with impaired glucose regulation and that there are sufficient numbers of patients with impaired glucose regulation who can be referred to the Care Call service and thus be invited to the CATFISH trial.

After triage, the diabetes specialist nurse at the Care Call service will pass details of all eligible patients to the CATFISH trial administrator. The CATFISH trial administrator will call all patients and confirm personal details (email and phone number). Each patient is given a brief overview of the CATFISH trial. The administrator will confirm that each patient meets the inclusion criteria for the CATFISH trial (access to home internet and a desktop computer or laptop), and will seek permission for the University of Manchester research team to contact them. Those patients who do not wish to be approached by researchers will be redirected to the existing Care Call service (IGR2). The contact details of those patients who do agree to be contacted will be passed to the University of Manchester research team using a secure (nhs.net) email service. Within one week, a University of Manchester researcher will then contact the patient to discuss involvement in the trial in greater detail, giving them an opportunity to ask questions about the trial.

### Participant timeline

The recruitment window runs from July 2015 to the end of June 2016. After consenting and undertaking baseline assessments, participants will enter the IGR3 or IGR2 service, where they will receive active therapeutic contacts for 6 months, followed by a step-down call at 9 months. We will collect measures at baseline, and 9 months (i.e. 3 months after the end of the core contact period; see Table 1). Recruitment flow and timelines of assessments are shown in Fig. 3 and Table 2, respectively.

**Fig. 3 Fig3:**
[figure not shown]
CONSORT flow diagram. UoM, University of Manchester

**Table 2 Tab2:**
[figure not shown]
SPIRIT Schedule of enrolment, interventions and assessments

*CSQ* Client Satisfaction Measure, *EQ-5D* EuroQol five dimensions, *HbA1c* glycated haemoglobin (A1c), *MHI-5* Mental Health Inventory, *PAM* Patient Activation Measure, *SDSCA* Summary of Diabetes Self-Care Activities

### Randomization and allocation concealment

On providing consent, participants will be asked to complete baseline assessments and are then randomized using a remote and automated randomization service provided by the Manchester Academic Health Science Centre Clinical Trials Unit (MAHSC-CTU) at the Christie Hospital NHS Foundation Trust, Manchester, UK. To ensure allocation concealment, randomization will be by means of a computer-generated code implemented by a MAHSC-CTU employee and shared by telephone with the Care Call administrator following correct exchange of a password. The Care Call administrator will communicate allocations to Care Call staff (diabetes specialist nurse and health advisors). Participants will be allocated 1:1 to either IGR2 or IGR3 using minimization to ensure balance for age (<40, 40–60, >60 years) and body mass index (≤18.5, 18.6–24.9, 25.0–29.9). We will use minimization with a probability weighting of 0.75 to reduce predictability.

### Blinding

It will not be possible to blind participants to treatments but they will not be formally told which intervention is an existing service (IGR2) and which intervention is novel (IGR3). Our researchers at the University of Manchester will be informed of the MAHSC-CTU randomization number for each participant by the Care Call administrator. The MAHSC-CTU randomization number will become the primary identifier for participants in the trial. In addition to the Care Call administrator, the principal investigator ([name]) will be unmasked to allocations in the event that participants request to be unblinded. Participants will be unblinded at the end of the follow-up period, or on withdrawal from the study. The CATFISH research team at the University of Manchester will remain blind to treatment allocation until follow-up assessments have been completed. The trial statistician will remain blind to treatment allocation. However, owing to the nature of health economic analysis, it is not possible to blind the trial health economist.

### Data collection

At the baseline assessment visit, University of Manchester researchers will record the height and weight of participants and calculate body mass index using the NHS Choices body mass index healthy weight calculator [41]. Height will be measured using a Leicester stadiometer on a firm and even surface. Participants will be asked to remove their shoes and stand up straight with heels together, with heels, buttocks and shoulders pressed against the stadiometer. The University of Manchester researcher will take the measurement with the participant standing tall, looking straight ahead with the head upright and not tilted backwards.

Where participants’ cannot stand, arm span can be used as an estimate of height, using the formula: total arm span/1.06 (women) or total arm span/1.03 (men). Arm span is measured by locating and marking the edge of the right collar bone (in the sternal notch) with a pen. Participants will each be asked to place their non-dominant arm in a horizontal position. The researcher will check that the patient’s arm is horizontal and in line with the shoulders. Using a tape measure, the researcher will measure the distance from the mark on the midline at the sternal notch to the tip of the middle finger. If the arm is flat and wrist is straight, the researcher will take a reading in centimetres and repeat the process for the dominant arm to calculate the total arm span.

Weight will be measured in kilograms using Seca 875 weighing scales (Class 111 calibrated medical scales) that conform to ISO 9001:2008. Both height and weight will be recorded on a case report form. The participant’s initials is entered onto the front cover of the case report form, along with general practitioner ‘P’ code and date of completion. After height and weight have been measured, participants will be given the baseline questionnaire to complete. Researchers will be available to answer any questions the participant may have during completion. Explanation should be given without biasing the participant’s response. The researcher may also read the questions and complete the questionnaire if the participant requests this. After completing the questionnaire, the researcher will check that all questions have been attempted.

At follow-up, the researcher will contact the participant by telephone to arrange a convenient time and place to meet for the follow-up assessment. During this, call the researcher will remind the participant not to tell the researcher if they were part of the telephone-only health coaching group or the web plus telephone health coaching group. At the follow-up assessment visit, the researcher will adopt the same procedures undertaken at the baseline visit to collect and record data on height and weight. The participants will be given the follow-up questionnaire to complete and the researcher will adopt the same procedure undertaken at the baseline visit to ensure that this questionnaire is completed appropriately.

After completing follow-up assessments, participants will be invited to attend an appointment at the Clinical Research Facility at Salford Royal NHS Foundation Trust for a plasma glucose test to measure HbA1c. All blood tests will be conducted by nursing staff at the Barnes Clinical Research Facility, Salford Royal NHS Foundation Trust. Sample type and volume are fluoride oxalate (yellow), 1 ml; the reference range is 3.0–6.0 mmol/l. Laboratory staff will follow the Salford Royal NHS Foundation Trust protocol for prevention and management of potential exposure to blood-borne viruses, including needlestick and sharps injuries [42].

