**Methods:**

CATFISH is a two-parallel group, single-centre individually randomized controlled trial. Eligible participants are patients aged ≥18 years with impaired glucose regulation (HbA1c concentration between 42 and 47 mmol/mol), have access to a telephone and home internet and have been referred to an existing telephone health coaching service at Salford Royal NHS Foundation Trust, Salford, UK. Participants who give written informed consent will be randomized remotely (via a clinical trials unit) to either the existing pathway (IGR2) or the new web-enhanced pathway (IGR3) for 9 months. The primary outcome measure is patient acceptability at 9 months, determined using the Client Satisfaction Questionnaire. Secondary outcome measures at 9 months are: cost of delivery of IGR2 and IGR3, mental health, quality of life, patient activation, self-management, weight (kg), HbA1c concentration, and body mass index. All outcome measures will be analyzed on an intention-to-treat basis. A qualitative process evaluation will explore the experiences of participants and providers with a focus on understanding usability of interventions, mechanisms of behaviour change, and impact of context on delivery and user acceptability. Qualitative data will be analyzed using Framework.

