However, current evidence of effectiveness is mixed. A systematic review of 13 randomized controlled trials or quasi-experimental studies showed that, in 11 studies, telephone, internet or a combination of telephone, face-to-face, internet or email health coaching can effectively improve physical and mental health, promote healthy behaviours and increase social support among people with long-term conditions [11]. Other reviews have similarly identified a number of effective models, although the important ‘active ingredients’ are not clear [12, 13]. Moreover, much of the evidence is derived from trials conducted in the USA and there is uncertainty about the benefits of health coaching in the UK. A recent evaluation of the nurse-led Birmingham OwnHealth telephone health coaching service for people with long-term conditions (including diabetes) did not find reductions in health service utilization or cost over 12 months [14]. By contrast, a UK trial of telephone support from non-clinical telecare staff (backed up by diabetes specialist nurses) did show significant improvements in glycaemic control in people with type 2 diabetes, compared with usual care [15]. This intervention, now known as Diabetes Care Call, has recently been adapted for use in people with impaired glucose tolerance and impaired glucose regulation. A pilot evaluation (*n* = 44) of the Care Call intervention in people with impaired glucose tolerance showed reductions in weight (2.81 kg, 95 % confidence interval 1.2–4.42), body mass index (1.06 kg/m^2^, 95 % confidence interval 0.49–1.63), and fasting blood glucose (0.29 mmol/l, 95 % confidence interval 0.07–0.51) 1 year after the intervention [16]. Similar outcomes 12 months after the intervention were achieved in a pilot evaluation of Care Call in people with impaired glucose regulation who were offered either a telephone-only or a telephone plus group education pathway [17]. While the findings of these pilot studies are limited by the absence of a control group, they offer proof of concept that telephone health coaching can translate to people with impaired glucose regulation to promote positive and sustained lifestyle changes to prevent type 2 diabetes.

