### Data management

After completion of blood tests and analysis, nursing staff at the Barnes Clinical Research Facility will be notified and will collect the results from the laboratory. Hard copies of the results will then be stored in a locked, secure area. A member of the CATFISH research team will visit the Barnes Clinical Research Facility at least once every two weeks to collect the results. The results will then be returned to the CATFISH office at the University of Manchester and stored securely.

Once the research team has collected the HbA1c concentration results from the Clinical Research Facility, they will be screened by the CATFISH Research Nurse. If the HbA1c concentration falls outside the normal prediabetes range expected (≥48 mmol/mol), the participant’s general practitioner will be informed by letter of the result. If the concentration remains within the prediabetes range (42–47 mmol/mol) or is within the normal range (<42 mmol/mol) the general practitioner will not be routinely informed of the result. Blood samples for HbA1c testing will be automatically archived after analysis to a secure storage unit in the pathology department at Salford Royal NHS Foundation Trust and kept at 4 °C. They will be kept for a maximum of 2 days and then sent for incineration.

Demographic and outcome data will be collected in an anonymized format using paper-based questionnaires administered face-to-face by the University of Manchester researchers. Additional data about engagement and delivery of the intervention will be captured by the secure and web-based system hosted by NorthWest EHealth at the University of Manchester. Patient confidentiality will be protected throughout all phases of data collection and analysis, in accordance with them UK Data Protection Act, 1998. The data management policy will adhere to Research Councils UK Common Principles on Data Policy and will be created by the principal investigator in accordance with the University of Manchester’s intellectual property policy and relevant third-party agreements. All paperwork will be transferred immediately to the University of Manchester and stored in a lockable fling cabinet. Paperwork with patient-identifiable data (consent form, case report form) should be stored separately from anonymized data (baseline and follow-up questionnaires).

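### The 9-month HbA1c measurement is described as a plasma glucose test in mmol/l, which contradicts the mmol/mol scale used for HbA1c in the rest of the protocol

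*Protocol article*

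**What the plan says.** Only the protocol article is at hand. Its Abstract lists the 9-month secondary outcomes, among them "weight (kg), HbA1c concentration, and body mass index", and the section on health outcome measures lists HbA1c again. Plasma glucose is not listed as an outcome.

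Data collection explains how the follow-up value is obtained. Participants are invited to a separate appointment "for a plasma glucose test to measure HbA1c", and the specimen is then described: "Sample type and volume are fluoride oxalate (yellow), 1 ml; the reference range is 3.0–6.0 mmol/l".

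Data management picks up the same results under another description. It speaks of what happens "Once the research team has collected the HbA1c concentration results from the Clinical Research Facility", and of storage: "Blood samples for HbA1c testing will be automatically archived after analysis". It sorts the results into <42, 42–47 and ≥48 mmol/mol and attaches an action to the top band: "If the HbA1c concentration falls outside the normal prediabetes range expected (≥48 mmol/mol), the participant’s general practitioner will be informed by letter". The samples are destroyed after no more than two days.

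The Abstract, Inclusion criteria, Exclusion criteria and Amendments sections all give HbA1c in mmol/mol.

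**The concern.** The sentence that defines the measurement names one analyte as the means of measuring another, and the unit that follows belongs to the first. This is more than one slipped word, because the test name and the reference range agree with each other and disagree with the rest of the article.

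If the Data collection text were followed literally, three things would be at stake:

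- **The HbA1c comparison.** Statistical analysis promises descriptive baseline and follow-up scores for most outcomes, adjustment for the baseline value of each outcome, and standardized effect sizes for all outcomes. None of this is meaningful if baseline is HbA1c and follow-up is glucose.
- **The imputation model.** The chained equations use scores on all primary and secondary outcomes. Glucose values labelled as HbA1c would enter that model, which also serves the CSQ-8.
- **The screening of results.** The ≥48 mmol/mol notification step would have no valid input.

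**Working it through.** The plan states no figure to reproduce here, so the check compares analyte and unit section by section.

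1. **What is to be measured.** HbA1c, as a secondary outcome (Abstract; health outcome measures).
2. **The scale used for HbA1c.** 42–47 mmol/mol, paired with 6.0–6.4 % (Inclusion criteria); ≥48 mmol/mol, paired with ≥6.5 % (Exclusion criteria); 42–47 mmol/mol (Amendments); <42, 42–47 and ≥48 mmol/mol (Data management).
3. **The scale used for glucose.** mmol/l. Background, under Health coaching, reports the pilot result as "fasting blood glucose (0.29 mmol/l", a measure in its own right.
4. **The test described at follow-up.** Plasma glucose, 3.0–6.0 mmol/l (Data collection). This matches step 3 and not step 2.

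**Can the result be carried onto the HbA1c scale?** The document gives no conversion. If the numbers were entered unchanged, the upper reference limit of 6.0 lies below 42, so every value in the reference range would fall in the <42 band. To reach the top band a value would have to be 48 / 6.0 = 8 times the upper reference limit. The notification step could not work as intended on such numbers.

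**Can 3.0–6.0 be read as HbA1c in per cent?** The article does pair 42 mmol/mol with 6.0 %, so the upper limit would fall at the lower edge of the prediabetes range. But the printed unit is mmol/l and the printed test is plasma glucose. Two separate errors would have to be assumed, and nothing in the text supports that reading.

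**Could results already exist?** Trial status dates the first recruitment to 30 June 2015. Adding 9 months gives about the end of March 2016 for the first follow-up. Recruitment was completed in May 2016 and data collection was to end by March 2017 at the latest. When the article was written, some results could therefore have been on file, with further samples still to be taken.

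**Could a wrong assay be repaired later?** Not from stored blood, since samples are kept for no more than two days.

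**The case against.** The strongest reply is that the protocol plainly means HbA1c. The disputed sentence itself says the purpose is to measure HbA1c. Data management refers to HbA1c results and to samples for HbA1c testing, and its bands make sense only for HbA1c. No section lists glucose as an outcome. A laboratory returning values near 5 to a team expecting values near 45 would probably be noticed. On this view, glucose test details were put in the place of the HbA1c details, and the fault lies in the description.

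Much of this stands. A reader might infer that the HbA1c outcome could not be obtained or was lost. The document does not support that: the two sections conflict, and neither shows which assay was run.

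The reply is also right about weight. HbA1c is one of several secondary outcomes, Sample size says the trial is not powered for these, and Statistical analysis commits to a formal test only for the CSQ-8.

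Two further inferences should be resisted. One is that the specimen tube itself rules out HbA1c; the document says nothing about which tube suits which assay. The other is a head count of affected results based on the 15 % attrition in Sample size. That rate was set for the CSQ-8 power statement, whereas the blood test is a separate, invited appointment whose attendance is not given.

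The reply does not remove the contradiction. The Data collection text is the only description of the measurement procedure, it is wrong as written for the outcome it serves, and no other section corrects it.

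**Conclusion.** The point holds as an internal contradiction about how a secondary outcome is measured. As described, the follow-up test yields a glucose concentration, which cannot be read against the mmol/mol bands or analysed as HbA1c. Whether this is an error of description or of procedure cannot be settled from the document, although Data management favours the former.

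If only the description is wrong, no data are affected and a corrected text ends the matter. If the assay is wrong, every follow-up value obtained with it is lost for HbA1c and cannot be recovered from stored blood. The number of such values cannot exceed the 209 participants randomized; the document gives no basis for a closer figure.

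The CSQ-8 is not measured by this test. The only route to the primary analysis is through the imputation model, where mislabelled glucose values would act as one predictor among many. The size of that effect cannot be derived from the document.

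The conclusion rests on the named analyte and the units alone.

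**What to change.** - **Reconcile the text.** Bring Data collection into agreement with the health outcome measures, Inclusion criteria and Data management sections on analyte, sample, unit and reference range, as actually run at the facility. The ≥48 mmol/mol notification step must refer to the same assay.
- **Check results on file.** Confirm from the laboratory reports which analyte was measured, before any analysis and before further samples are taken.
- **If any results are plasma glucose,** report them as glucose, treat HbA1c as missing for those participants, do not convert, and keep the glucose values out of the HbA1c analysis and the imputation model. If no follow-up HbA1c was observed at all, report the outcome as not measured, since there would be nothing from which to impute it.

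**Cost.** If only the description is wrong, a text correction and a review of the stored hard copies. If a wrong assay is found, checking files identifies the lost HbA1c values but cannot restore them; only samples not yet taken would benefit.
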